### Assessment of variables

At the onset and end of the trial, body weight and height will be measured to the nearest 0.1 kg and 0.1 cm using the Seca scale and stadiometer (Seca), respectively. Individuals will be measured barefoot and wearing light clothing. BMI for age *Z*-score is computed by dividing weight in kilograms by height in meters squared according to age in the curve standard using WHO growth standards (www.who.int/childgrowth). A 24-h dietary recall, a valid instrument for the evaluation of diet, will be completed by patients at the beginning and end of intervention in face-to-face interviews and used for dietary assessment. Information about dietary consumption will be analyzed using Nutritionist IV software. The physical activity questionnaire for children (PAQ-C) and physical activity questionnaire for adolescents (PAQ-A) which have been validated in Iran will be applied to estimate participant physical activity levels. The PAQ-C which is appropriate for ages 8–14 provides a physical activity score derived from 9 items, each scored on a 5-point scale. The PAQ-A, which is appropriate for ages 14–20, provides a physical activity score derived from 8 items, each scored on a 5-point scale. Physical activity will be reported in three categories, namely low activity, moderate activity, and high activity levels, based on the PAQ-A scoring protocol [18, 19]. Blood pressure will be measured using a mercury sphygmomanometer after at least 5 min of resting. The measurement will be taken on two occasions, and the mean of the two will be considered as the individual’s blood pressure.

Blood samples (10 mL) will be drawn following 12-h overnight fasting and centrifuge at 3000 rpm for 5 min to extract serum samples pre-and post-intervention. The concentrations of TC, TG, and HDL-C will be evaluated using commercial kits (DIALAB Inc. kit, Vienna, Austria) before and after the intervention. Serum LDL-C values will be calculated using the Friedewald formula. The concentrations of FBI and FBS will be measured using commercial enzyme-linked immunosorbent assay (ELISA) kit (IBT, USA) and glucose oxidase method, respectively. HbA1c will be assessed using commercial kit (BioRex Inc., Tehran, Iran) by auto-analyzer (Mindray auto hematology analyzer). Moreover, BUN and creatinine will be examined by diacetyl monoxime method and enzymatic method, respectively. ESR will be evaluated by Westergren method using a special tube. In addition, serum hs-CRP levels will be assessed using ELISA kit (Paadco Inc. kit, Tehran, Iran) pre-and post-intervention. Also, the following formulas will be used to determine QUICKI and HOMA-IR. Proteinuria will be evaluated by albumin dipstick through collecting urine samples.

QUICKI: 1/(log (fasting insulin μU/ml) + log (fasting glucose mg/dl))

HOMA-IR: [fasting insulin (μU/ml) × fasting glucose (mg/dl)]/405

FMD and CIMT will be assessed by an expert radiologist. For evaluating FMD, after an overnight fasting and 10 min rest, patients will lie down in the supine position in a quiet, temperature-controlled room and put their right hand in a comfortable position on a surface for imaging the brachial artery. Ultrasound imaging of the brachial artery will be done by Doppler ultrasound (Samsung Medison UGEO H60, Seoul, South Korea) and in longitudinal section, 2 cm above of antecubital fossa. An anterior and posterior section will be selected between the lumen and the vessel wall for clear imaging, and after that, the diameter of vessel will be measured from the anterior part to the posterior part between Media and Adventitia. A baseline rest image will be acquired and the arterial diameter will be measured. For the second scan, the cuff of the sphygmomanometer will be closed around the arm and a 5-minute occlusion of at least 50 mm Hg above the systolic pressure will be applied to the vessel. Finally, 90 seconds after the cuff will be opened, the second measurement will be performed. The following formula will be used to calculate FMD, where d1 is the baseline brachial artery diameter and d2 is brachial artery diameter after 90s of cuff release.

FMD: (d2 − d1) × 100/d1

To assess CIMT, the thickness of two inner layers of Intima and Media artery will be measured by Doppler ultrasound (Samsung Medison UGEO H60, Seoul, South Korea). The distance between the main edge of the first line and the main edge of the second line in the carotid artery will be considered as CIMT. To increase the accuracy, all measurements will be repeated for 4 times.

### Data management and monitoring

A clinical trial monitor will occasionally supervise the study progress and ensure that patient rights and well-being are safeguarded. The clinical trial monitor will also supervise that the protocol, ethical requirements, standards, and regulations are being followed, the essential documentation is available, and collected data is accurately recorded. One of the researchers will check the coding, security, and storage of data. In addition, he/she will evaluate data entry and data values twice. If any participant reports the occurrence of adverse events, more information is required to make decision about excluding the participants from the trial. Unblinding is permissible in this situation based on the Medical Ethics Committee criteria [20].

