## Material and methods

### Study population

Adolescents with type 1 diabetes will be recruited from Mofid Children’s Hospital, Tehran, Iran, by an investigator. The investigator will conduct study assessments and screen study patients. The patients will be diagnosed by a specialist. It should be noted that because of the simultaneous occurrence of the coronavirus disease 2019 (COVID-19) pandemic and implementation of this study, researchers should expand their presence time in Mofid Children’s Hospital for achieving adequate participant enrollment to reach the target sample size. Patients that satisfy the inclusion criteria will be eligible to participate in this research. The inclusion criteria are considered as follows: adolescents aged between 10 to 18 years, whose body mass index (BMI) for age *Z*-score ranges between 5 and 85%, diagnosis of type 1 diabetes by a specialist, receiving insulin therapy, at least 5 years have passed since the diagnosis of type 1 diabetes, and a signed written informed consent form for participation in this trial. The exclusion criteria include subjects who are pregnant or breastfeeding, those affected by endocrine, metabolic, blood clotting, or any acute disorder, and patients who had diabetic ketoacidosis or hypoglycemia (blood sugar level lower than 50 mg/dl) in the last 12 or 3 months, respectively. In addition, subjects who consumed antihypertensive, anti-inflammatory, anticoagulant, lipid-lowering, and weight-lowering agents and antioxidant and omega-3 supplements in the last 6 months prior to the study will be excluded. Patients with fish or seafood allergies and smokers will also be excluded. Participants who are unwilling to continue collaborating on the trial or have poor compliance (less than 80%) with the assigned intervention will be withdrawn from follow-up.

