### Intervention

Sixty eligible adolescents with type 1 diabetes will be randomly assigned to the omega-3 (*n* = 30) and placebo groups (*n* = 30). Omega-3 capsules (600 mg) and identical placebo capsules will be respectively taken by patients in the intervention and control group once a day, for 12 weeks. The Karen Pharma & Food Supplement company will provide omega-3 capsules. Omega-3 and placebo capsules will be similar in weight, size, shape, taste, color, and odor. Placebo capsules will be also produced by Karen Pharma & Food Supplement company and contain 600 mg oral glycerin. Naringenin and placebo capsules will be given to the study patients for every one month in study visits. There are four study visits in our trial (before the intervention, after 1 month of intervention, after 2 months of intervention, and at the end of the intervention). Study patients will be informed how to use their supplements, and they will be weekly followed by phone calls. Compliance will be evaluated based on unused supplements by each person. The remaining capsules will be counted to determine total supplement intake. Furthermore, patients will be asked about any adverse events experienced following omega-3 consumption. If the reported adverse events are related to omega-3 consumption, participants will be asked to stop taking supplements, and they will be immediately referred to a specialist for therapy. It should be noted that there will be no dietary recommendation or dietary regimen for study patients.

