### Sample size calculation

Considering a type I error of 5%, a power of 90%, and the changes in FMD values as one of the primary outcomes [17], the sample size was computed to be 25 for each study group based on the two-sided t-test. To compensate for an approximate attrition rate of 20% throughout the research, we rise the final sample size to 30 adolescents in each group.

$$ n=\frac{{\left({Z}_{1-\alpha /2}+{Z}_{1-\beta}\right)}^2\times \left({S}_1^2+{S}_2^2\right)}{d^2} $$

(*α* = 5%, 1-β = 90%, *SD*_1_ = 2.7, *SD*_2_ = 2.7, *d* = 2.5)

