### Outcomes

The primary outcome of the current trial is the alteration in the value of FMD as an endothelial function marker at the end of the trial compared to the baseline value. Alterations in carotid intima-media thickness (CIMT), anthropometric indices including weight, height, and BMI for age *Z*-score, lipid profile including triglyceride (TG), high-density lipoprotein cholesterol (HDL-C), low-density lipoprotein cholesterol (LDL-C), and total cholesterol (TC), glycemic parameters including fasting blood sugar (FBS), hemoglobin A1C (HbA1C), fasting blood insulin (FBI), hemostatic model assessment of insulin resistance (HOMA-IR), and quantitative insulin sensitivity check index (QUICKI), plasma levels of high-sensitivity C-reactive protein (hs-CRP) and erythrocyte sedimentation rate (ESR), blood pressure, BUN, creatinine, proteinuria, energy intake, and consumption of nutrients are considered as secondary outcomes. Furthermore, at the beginning of the research, medical history and demographic factors including age, sex, race, education level, and marital status will be asked from all the patients or their legal guardians.

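### Low compliance ends follow-up and an adverse event can end participation, so patients removed before the final visit have no 12-week FMD and the primary comparison can be biased even while the blind holds

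*Protocol article*

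**What the plan says.** Two rules in the protocol article can take a randomised patient out of the trial.

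- **Low compliance (Study population).** Patients who "have poor compliance (less than 80%) with the assigned intervention will be withdrawn from follow-up". The wording is mandatory, and what ends is follow-up, not only the capsules.
- **Adverse events (Data management and monitoring).** "If any participant reports the occurrence of adverse events, more information is required to make decision about excluding the participants from the trial". This is a discretionary decision, but it concerns participation in the trial. The next sentence adds: "Unblinding is permissible in this situation based on the Medical Ethics Committee criteria".

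The Intervention section has a separate rule on treatment: "If the reported adverse events are related to omega-3 consumption, participants will be asked to stop taking supplements", with referral to a specialist.

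The primary outcome (Outcomes) is "the alteration in the value of FMD as an endothelial function marker at the end of the trial compared to the baseline value". The Abstract places the FMD assessment at baseline and end of trial, with no interim measurement. Capsules are taken "once a day, for 12 weeks". The four visits are before the intervention, after 1 month, "after 2 months of intervention, and at the end of the intervention". Statistical analysis compares between-group changes by t-test or Mann-Whitney test, which needs the final value.

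**The concern.** Randomisation protects the comparison only for the patients who were randomised. Both rules select patients on something that happens afterwards and that the capsule itself may influence, whether that capsule is omega-3 or the glycerin placebo. If one capsule is less well tolerated or less readily taken, more patients leave that arm. If those who leave would have had a different FMD change from those who stay, the difference among the remaining patients no longer estimates the effect in all 60.

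Nobody has to know the allocation for this to happen, so the double blind does not prevent it. A statistical analysis plan not shown here cannot repair it either, because no analysis recovers an FMD value that was never measured.

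**Working it through.** **1. The plan's own figure.** Inputs from Sample size calculation: two-sided α = 5%, power 90%, SD 2.7 in both arms, d = 2.5.

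n = (1.960 + 1.282)² × (2.7² + 2.7²) / 2.5² = 24.5, rounded up to 25 per arm. This matches the protocol, which then raises it to 30: "To compensate for an approximate attrition rate of 20% throughout the research".

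**2. When a compliance withdrawal costs the outcome.** One capsule a day for 12 weeks is 12 × 7 = 84. If the full course is the denominator (assumed), 0.80 × 84 = 67.2. A patient who takes 67 or fewer is then below the limit (67/84 = 79.8%; 68/84 = 81.0%), having missed 17 or more.

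- Already 17 or more missed at the 1- or 2-month visit: withdrawal can come before the final visit, and there is then no 12-week FMD.
- Below 80% only at the final count: the 12-week FMD may already exist.

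The outcome is therefore lost for certain only when removal comes before the final visit. The same holds for exclusion after an adverse event.

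**3. Size of the bias (illustration).** The documents give no adverse-event or non-compliance rate by arm and no link from either to FMD, so every input here is assumed. Suppose m of 30 are removed in one arm and none in the other, and the removed patients' mean FMD change would have differed from that of the patients kept by k SD.

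The full-arm mean differs from the mean of those kept by (m/30) × k × 2.7.

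- m = 1, k = 0.5: (1/30) × 1.35 = 0.045 points, and 0.045/2.5 = 1.8%.
- m = 3, k = 1: (3/30) × 2.7 = 0.27 points, and 0.27/2.5 = 10.8%.

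With removal in both arms the bias is the difference between the two arms' terms, so it is zero if removal and prognosis are the same in both.

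On the test: the standard error is 2.7 × √(1/29 + 1/30) = 0.703 in the first case and 2.7 × √(1/27 + 1/30) = 0.716 in the second. The shifts are 0.06 and 0.38 standard errors. The two-sided type I error (noncentral t) is then 5.05% and 6.6% instead of 5%.

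**4. What keeping these patients does to power.** Assume m of 30 omega-3 patients stop capsules and gain nothing. The expected difference is 2.5 × (1 − m/30). Mixing stoppers and non-stoppers raises the omega-3 arm variance to 2.7² + p(1 − p) × 2.5², with p = m/30. If 20% of 30 are still lost for other reasons, 30 − 6 = 24 per arm remain. Power is for the two-sided t-test (noncentral t); each cell gives SD 2.7, then the value with the extra variance.

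| m | Difference | 30 per arm | 24 per arm |
|---|---|---|---|
| 0 | 2.50 | 94.1% | 88.1% |
| 1 | 2.42 | 92.6% / 92.3% | 85.9% / 85.4% |
| 2 | 2.33 | 90.8% / 90.1% | 83.4% / 82.4% |
| 3 | 2.25 | 88.8% / 87.6% | 80.7% / 79.2% |

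**The case against.** The strongest reply is that the loss is narrow and the effect small. Compliance is judged by counting returned capsules, and the full count is known only at the final visit, where FMD is also measured. The adverse-event sentence excludes nobody by itself: it asks for more information before a decision, and does not say that outcome collection stops. Nothing in the article suggests that the two capsules, matched on size, taste and odour, are tolerated differently. Even the illustrated shift is well under half a standard error.

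Much of this stands, and it rules out several stronger readings that a reader might infer.

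- *Every patient below 80% lacks a 12-week FMD.* Not supported, as step 2 shows. Whether an FMD already measured is used is a matter commonly left to the analysis plan.
- *Any adverse event means exclusion.* Not supported. The decision is discretionary, and the compliance rule is the firmer of the two.
- *Stopping capsules for safety leads automatically to withdrawal for poor compliance.* This would follow from a literal reading of the two rules together, but no section says how an instructed stop is counted.
- *The decision on participation is taken unblinded.* The article permits unblinding under Ethics Committee criteria that are not shown. It does not say that a code break comes first, and unblinding for an adverse event is an ordinary safety provision.
- *The 20% attrition allowance measures the bias.* Six of 30 removed selectively in one arm would give 0.27 to 0.54 points on the same assumptions. But that figure is a general allowance, not a forecast of removal under these rules or of an imbalance between arms.

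What the reply does not answer is the early case. The compliance rule says in plain words that follow-up ends, and it can apply at the 1- or 2-month visit.

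**Conclusion.** The point holds in this limited form. One stated rule ends follow-up for low compliance and another allows exclusion after an adverse event. A patient removed under either before the final visit has no primary outcome, and because both triggers arise after randomisation, the remaining groups may not be comparable even if the blind is intact.

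The bias is possible, not certain, and neither its direction nor its size can be derived from the documents. The range of 0.045 to 0.27 points rests wholly on assumptions: 1 to 3 of 30 removed in one arm only, and a 0.5 to 1 SD difference in their FMD change. On those inputs the effect is modest. The case for change is that the loss is created by rule and is cheap to avoid, not that it is shown to be large.

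**What to change.** Amend Study population so that compliance below 80% is recorded, and may affect capsule intake, but does not end follow-up. Amend Data management and monitoring to match, so that an adverse event leads to a decision on capsules only. In both cases obtain the 12-week FMD at the planned final visit unless consent is withdrawn, and include it in the randomised arm. Stopping capsules, specialist referral and unblinding for care stay as they are.

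The cost is a protocol amendment after recruitment began on 20 May 2021. No new visit and no larger sample are needed. The effect is slightly diluted: under the assumptions in step 4 with 1 to 3 stoppers, power is about 93% to 88% with 30 per arm (94% undiluted). It is about 86% to 79% with 24 per arm if 20% attrition still occurs for other reasons (88% undiluted).

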### Statistical analysis

Statistical analysis of all data will be done by SPSS statistical software (SPSS Inc., Chicago, IL, USA, version 24), and *P* values less than 0.05 will be considered statistically significant. The Kolmogorov-Smirnov test will be used for assessing the normality of the data. Quantitative and qualitative variables will be presented as mean (standard deviation) or median (25th–75th percentile) and frequency (percentage), respectively. To examine differences in qualitative variables between omega-3 and placebo groups, we will apply the chi-square test. We will use the independent sample *t*-test or Mann-Whitney *U* test to determine differences in numerical variables between the omega-3 and placebo groups. In addition, aforementioned tests will be used to compare between-group alterations in outcome variables. To do within-group comparison, we will use the paired-sample *t*-test or its nonparametric equivalent, the Wilcoxon test. General linear model will be applied to adjust the effects of confounding factors. To control confounders and strengthen our findings, any alterations in dietary intakes and physical activity levels will be taken into consideration throughout the trial.

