### Randomization and blinding

After obtaining the informed consent and discussing the objectives of the research, eligible subjects (*n* = 60) will be divided into two equal groups, stratified by sex and the amount of daily insulin intake using stratified block randomization, with 1:1 allocation ratio. The block randomization will be conducted by an assistant and the intervention allocation will be blinded for both the investigators and participants. The sequence of the blocks will be prepared for each stratum using a random numbers table. All patients are randomly allocated to an intervention (Omega-3) group or a placebo group. The manufacturer who is responsible for preparing the supplements will be asked to assign a unique code on the cans containing omega-3 or placebo.

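### The stated between-group test of FMD change uses neither baseline FMD nor the randomisation factors as covariates, and the general linear model has no fixed role: a loss of precision, not a bias

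*Protocol article*

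**What the plan says.** - **Outcome.** The Outcomes section makes the change in FMD from baseline to the end of the trial the primary outcome.
- **Sizing.** In Sample size calculation, "the sample size was computed to be 25 for each study group based on the two-sided t-test", with SD 2.7 in each group and a difference of 2.5. It does not say whether 2.7 is the SD of change or of a single FMD value.
- **Attrition.** "To compensate for an approximate attrition rate of 20% throughout the research, we rise the final sample size to 30 adolescents in each group".
- **Randomisation.** Patients are "stratified by sex and the amount of daily insulin intake using stratified block randomization" (Randomization and blinding). The number of insulin categories is not given.
- **Test.** In Statistical analysis, "The Kolmogorov-Smirnov test will be used for assessing the normality of the data". Numerical variables are then compared by independent t-test or Mann-Whitney U, and "aforementioned tests will be used to compare between-group alterations in outcome variables".
- **Adjustment.** The same section applies a general linear model for confounding factors, without naming its outcome or saying whether it is primary or supportive. The next sentence names changes in diet and physical activity during the trial. No analysis sentence mentions baseline FMD, sex or insulin dose as a covariate.

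**The concern.** A change score uses the baseline, but with its coefficient fixed at 1. When the baseline-to-end correlation is below 1, a model that estimates the coefficient leaves less residual variance and also corrects for chance imbalance in baseline FMD. With 60 adolescents there is little precision to spare, and the data needed are collected anyway.

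The randomisation factors raise a second, smaller matter. If sex or insulin dose predicts FMD change, stratification balances them between arms, but a t-test that omits them still counts their variance as error.

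Third, it is not settled which result answers the primary question. The t-test and Mann-Whitney do not target the same quantity, the choice between them follows a normality check, and the general linear model stands beside both without a rank. The adjustment variables that are named could themselves be affected by treatment; energy and nutrient intake are listed as secondary outcomes.

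**Working it through.** **Inputs from Sample size calculation:** two-sided alpha 0.05, power 0.90, d = 2.5, SD = 2.7 per group, 25 per group raised to 30, attrition 20%. **Assumed:** baseline-to-end correlation r (not given, so a range is shown) and equal FMD variance at both times.

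**1. The plan's own figure.** n = (1.960 + 1.282)² × (2.7² + 2.7²) / 2.5² = 24.51, rounded up to 25. It reproduces. With 20% attrition, 30 × 0.80 = 24 per arm remain. Noncentral-t power of the t-test is 89.4% at 25 per arm and 88.1% at 24.

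**2. Variance formulas.** With σ the SD of a single FMD value, the change has variance 2σ²(1 − r) and the ANCOVA residual has variance σ²(1 − r²). The ratio is (1 + r)/2.

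**3. If 2.7 is the SD of change.** The ANCOVA SD is 2.7 × √((1 + r)/2). With 24 per arm and one degree of freedom spent on the covariate:

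| r | variance ratio | ANCOVA SD | t-test power | ANCOVA power |
|---|---|---|---|---|
| 0.3 | 0.65 | 2.18 | 88.1% | 97.3% |
| 0.5 | 0.75 | 2.34 | 88.1% | 95.2% |
| 0.7 | 0.85 | 2.49 | 88.1% | 92.6% |
| 0.8 | 0.90 | 2.56 | 88.1% | 91.1% |
| 0.9 | 0.95 | 2.63 | 88.1% | 89.6% |

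Spending four degrees of freedom instead of one costs less than 0.1 point.

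**4. If 2.7 is the SD of a single FMD value.** The change SD is 2.7 × √(2(1 − r)) and the ANCOVA SD is 2.7 × √(1 − r²). With 25 per arm:

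| r | change SD | ANCOVA SD | t-test power | ANCOVA power |
|---|---|---|---|---|
| 0.3 | 3.19 | 2.58 | 77.4% | 91.9% |
| 0.4 | 2.96 | 2.47 | 83.4% | 93.8% |
| 0.5 | 2.70 | 2.34 | 89.4% | 95.9% |
| 0.6 | 2.41 | 2.16 | 94.8% | 98.0% |

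**5. Strata.** If balanced strata explain a share R² of the variance of change, the t-test's standard error is too large by a factor of about 1/√(1 − R²). The true two-sided type I error is then about 2 × [1 − Φ(1.96/√(1 − R²))]: 4.4%, 3.9%, 2.8% and 1.9% at R² = 0.05, 0.10, 0.20 and 0.30. Simulation with four balanced strata and 24 per arm gives the same values. A separate simulation with 52 patients in four equal strata (d = 2.5, total SD 2.7) gives power of 93.0% unadjusted versus 93.2% adjusted at R² = 0.10, 94.3% versus 95.5% at 0.20, and 95.8% versus 97.4% at 0.30. The R² values and the four strata are assumptions.

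**The case against.** The strongest reply is that outcome, sizing and test agree: all three concern change in FMD and a two-sample t-test. Under randomisation that test is unbiased, and if 2.7 is the SD of change its power is close to plan. This stands, and it limits the point to efficiency and to naming one analysis.

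A second reply is that adjustment is planned, and that a journal article may leave the covariate list to the full protocol or analysis plan. This stands in part. The missing list is not itself a fault. But the article does state which test compares changes between groups, and that test has no covariates; the general linear model does not displace it, because its role is not stated.

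Third, the t-test or Mann-Whitney choice follows a check declared in advance, and the sizing points to the t-test for FMD. That is fair: the choice is not open-ended. It can still move the primary result from a difference in means to a rank comparison.

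A reader might infer more than the documents support:

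- **That baseline FMD is ignored.** It is subtracted; it is only not a covariate.
- **That omitting the strata raises the false-positive risk.** The effect runs the other way. It is also modest unless the strata explain much of the variance of change, and stable differences in FMD level are already subtracted out.
- **That the trial is underpowered.** This depends on what 2.7 describes and on a correlation that is not given. On the single-value reading the t-test falls clearly short at r = 0.3 or 0.4, but not at 0.6.

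**Conclusion.** The point holds as a matter of efficiency and clarity. The stated test is valid but less precise than an ANCOVA on data the trial already collects, and no sentence fixes how the general linear model relates to it.

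If 2.7 is the SD of change, ANCOVA adds between 9.2 points of power (97.3% − 88.1%, r = 0.3) and 1.5 points (89.6% − 88.1%, r = 0.9) at 24 per arm. If 2.7 is the SD of a single value, it adds between 14.5 points (91.9% − 77.4%, r = 0.3) and 3.2 points (98.0% − 94.8%, r = 0.6) at 25 per arm. The direction is secure; the size rests on equal variances and an unknown correlation. Nearly all of the gain comes from baseline FMD. Adjusting for the strata restores the nominal error rate and adds about 0 to 2 points of power under the assumed R² values. The change is worth making, but nothing here invalidates the planned comparison.

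**What to change.** Name one primary analysis: an ANCOVA of 12-week FMD on treatment, baseline FMD, sex and baseline daily insulin. Report the adjusted mean difference with its 95% CI whatever the Kolmogorov-Smirnov test shows. Keep changes in diet and physical activity after randomisation out of this model; if wanted, examine them in a separate, labelled supportive analysis. Keep the t-test and Mann-Whitney on change as sensitivity analyses. State in the sample size section whether 2.7 is the SD of change or of a single FMD value.

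The cost is wording. The variables are already collected, a general linear model in SPSS is already planned, and no patients or visits are added. The extra degrees of freedom cost less than 0.1 point of power.

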### Strengths and weaknesses

The strengths of the present study include using a randomized, double-blind, placebo-control design and also examining the effects of omega-3 supplementation on endothelial function indices and metabolic parameters in adolescents with type 1 diabetes for the first time. Also, as type 1 diabetes is a major health problem, thus there is a need to explore promising therapeutic agents for the management of the illness and its comorbidities. However, there are some weaknesses in this research. First, despite consideration given to any alteration in dietary intake or physical activity for statistical analysis, participants' self-reporting dietary intake and physical activity may impact the results. Second, no compliance biomarker for omega-3 intake will be measured. Finally, it might be advisable for the duration of omega-3 supplementation to be longer in order to observe an effect on study biomarkers. It is hoped that this trial will provide scientific evidence in support of omega-3 intervention for the management of type 1 diabetes and its consequences in adolescents suffering from the disease.

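### The general linear model appears set to adjust the omega-3 effect for changes in diet and physical activity during the trial, which arise after randomisation and cannot be confounders

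*Protocol article*

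**What the plan says.** The Statistical analysis section of the protocol article plans two kinds of between-group comparison. The first is an independent-sample t-test or Mann-Whitney U test on the changes in the outcomes. The second is a general linear model to adjust for confounding factors. That sentence lists no covariates. The next one, whose stated aim is to control confounders and make the findings stronger, says that "any alterations in dietary intakes and physical activity levels will be taken into consideration throughout the trial".

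Three other places bear on this:

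- Strengths and weaknesses describes the self-report limitation as remaining "despite consideration given to any alteration in dietary intake or physical activity for statistical analysis", so the changes are meant to enter the analysis.
- Outcomes states that "energy intake, and consumption of nutrients are considered as secondary outcomes". Physical activity is not in that list.
- Assessment of variables says the 24-hour dietary recall "will be completed by patients at the beginning and end of intervention in face-to-face interviews". Physical activity is measured separately, by the PAQ-C and PAQ-A questionnaires.

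No baseline covariate is named for the model: neither baseline FMD nor the two stratification factors in Randomization and blinding (sex and daily insulin intake).

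**The concern.** A change from baseline to the end of the trial contains a value measured on treatment. Randomisation already deals with confounding by baseline characteristics, and something that happens after allocation cannot confound the comparison of the allocated groups.

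Such a change can, however, be affected by treatment. If it is, and it also influences FMD, conditioning on it removes part of the treatment effect. If it shares unmeasured causes with FMD, conditioning on it opens a non-causal path between arm and outcome. In either case the adjusted coefficient stops estimating the total effect of assignment to omega-3.

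The article itself allows for an effect of treatment on diet, because it lists energy and nutrient intake as outcomes. The same variables are thus treated as responses to the intervention and as confounders of it. At stake is the adjusted estimate for FMD, the primary outcome, and for any other outcome analysed with the same model.

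**Working it through.** **1. The plan's own figure.** Sample size calculation uses α = 5% two-sided, power 90%, SD 2.7 in each arm and a difference of 2.5:

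n = (1.960 + 1.282)² × (2.7² + 2.7²) / 2.5² = 10.51 × 14.58 / 6.25 = 24.5, rounded up to 25 per arm.

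This reproduces the stated 25. The sample size is not in question. The step matters because it supplies the scale (SD 2.7, effect 2.5) and shows that the trial was sized for the unadjusted test: "the sample size was computed to be 25 for each study group based on the two-sided t-test".

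**2. Size of the shift in the adjusted estimate.** Let treatment move the covariate change by *a* SD, and let FMD change have a within-arm standardised slope *s* on that covariate. Then

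unadjusted minus adjusted estimate = a × s × 2.7.

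The documents give neither *a* nor *s*. The values below are assumptions, with zero included.

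| a (SD) | s | Shift in FMD points | Share of 2.5 |
|---|---|---|---|
| 0 | any | 0 | 0% |
| 0.3 | 0.3 | 0.3 × 0.3 × 2.7 = 0.24 | 10% |
| 0.3 | 0.5 | 0.3 × 0.5 × 2.7 = 0.41 | 16% |
| 0.5 | 0.3 | 0.5 × 0.3 × 2.7 = 0.41 | 16% |
| 0.5 | 0.5 | 0.5 × 0.5 × 2.7 = 0.68 | 27% |

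If *a* and *s* have the same sign, the adjusted estimate falls. If their signs differ, it rises.

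**3. Simulation check.** Two arms of 25 and SD 2.7 were simulated, with 3,000 runs per scenario and linear models with and without the covariate change. Three structures were used: a pure mediator (1 FMD point per SD of the covariate), a pure unmeasured common cause (loading 0.5 on both variables), and both together. Their within-arm slopes are 1.00, 0.5 × 0.5 × 2.7 = 0.675, and 1.675 FMD points per SD.

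| a (SD) | Adjusted estimate, true total effect 2.5 | Predicted: 2.5 − a × slope | Adjusted rejection rate at 5%, true total effect 0 |
|---|---|---|---|
| 0 | 2.50 to 2.53 | 2.50 | 0.04 to 0.05 |
| 0.25 | 2.09 to 2.33 | 2.08 to 2.33 | 0.06 to 0.10 |
| 0.5 | 1.68 to 2.17 | 1.66 to 2.16 | 0.08 to 0.27 |
| 1.0 (extreme) | 0.83 to 1.84 | 0.83 to 1.83 | 0.12 to 0.66 |

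The unadjusted estimate stayed between 2.49 and 2.52 in every scenario with a true effect of 2.5, with power 0.88 to 0.91. With no true total effect, its rejection rate stayed at about 0.05. The simulation agrees with the formula: the problem exists only when *a* is not zero, and only in the adjusted model.

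**The case against.** Five points can be made on the other side.

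- **An unadjusted test is planned.** It comes first in the Statistical analysis section, it is the test the sample size was computed for, and it is unaffected. This stands. A reader might infer that the trial's main FMD result is biased, but the article does not support that.
- **Nothing gives the adjusted result precedence.** Because the adjustment is said to make the findings stronger, a reader might infer that it would be preferred if the two analyses disagreed. No section says so, and the wording fits a supportive analysis equally well. What remains is that the role of each analysis is not stated.
- **The wording is loose.** Taking changes into consideration is not literally the same as entering them as covariates. That reading rests on the preceding general linear model sentence and on Strengths and weaknesses. It is the natural reading, but still an inference.
- **A shift caused by treatment may be small or absent.** The trial is double-blind, the capsules are alike in appearance, taste and odour, and no dietary advice is given. An observed difference of about 0.3 SD could also be chance, since its standard error is √(2/30) = 0.26 to √(2/25) = 0.28 SD. Adjusting for a chance difference is not the bias described here. This stands, and it is why zero belongs in the range.
- **Measurement error.** A reader might add that a single self-reported recall at each end makes the covariate noisy. That applies to diet only, and a noisy covariate that treatment does not affect does not bias the treatment estimate. The article already concedes the self-report limitation. This carries no weight in the point.

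A separate analysis plan may hold the full covariate list. The point does not depend on that list being absent. It concerns the one set of factors the article does name as the means of controlling confounding.

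**Conclusion.** The point holds as a flaw in a stated analysis choice. On the natural reading, the general linear model would condition on changes that arise after randomisation, some of which are the trial's own secondary outcomes. Those changes cannot be confounders of the randomised comparison. If treatment affects them, the adjusted estimate is not the total effect of assignment.

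The size is hypothetical: nil with no shift, and 0.24 to 0.68 FMD points (10 to 27% of 2.5) under the assumed shifts and slopes of 0.3 to 0.5. The point does not establish that bias will occur, that the unadjusted comparison is affected, or that a biased result would be favoured.

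It should be fixed, because the text leaves open which analysis supports the conclusion and the correction is nearly free. It does not undermine the design or the sample size.

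**What to change.** Amend the Statistical analysis section as follows:

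1. Restrict the general linear model for treatment effects to values fixed before randomisation: the baseline value of the outcome, sex, and daily insulin intake as used for stratification. Baseline diet and activity may be added if wanted. Fix the list before unblinding.
2. Report changes in diet by arm as the secondary outcomes they are, and changes in physical activity by arm descriptively.
3. Label any model that includes on-trial changes in diet or activity as exploratory, and state that it does not replace the unadjusted or baseline-adjusted comparison.
4. State which analysis of FMD change carries the conclusion.

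The cost is a few sentences. The plan already collects the values needed, and neither the sample size nor patient burden changes.
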